# POstLAparoscopic Reduction of pain By combining intraperitoneal normal salinE And the pulmonary Recruitment maneuver (POLAR BEAR trial). RCT to estimate reduction in pain after laparoscopic surgery when using a combination therapy of intraperitoneal normal saline and the pulmonary recruitment maneuver

**DOI:** 10.1186/s12905-017-0397-8

**Published:** 2017-06-13

**Keywords:** Postlaparoscopic pain, Shoulder pain, Pulmonary recruitment maneuver, Intraperitoneal saline

## Abstract

**Background:**

Shoulder pain and pain in the upper abdomen are common complaints after laparoscopy, sometimes surpassing the pain at incision sites. The incidence of shoulder pain ranges from 35 to 80%. Post-laparoscopic pain is caused by retention of carbon dioxide in the abdomen, which irritates the phrenic nerve and diaphragm, causing referred pain in the shoulder and in the upper abdomen. A promising strategy to reduce this post-laparoscopic pain is the pulmonary recruitment maneuver, which indirectly increases intraperitoneal pressure and thereby facilitates removal of residual carbon dioxide. An alternative strategy is the infusion of intraperitoneal normal saline. With normal saline infusion, carbon dioxide rises and escapes through the port sites. In addition, normal saline offers a physiologic buffer system to dissolve excess carbon dioxide.

**Methods/Design:**

This multicenter randomized controlled trial is conducted in two teaching hospitals in the Netherlands. Women between 18 and 65 years of age, with an ASA classification of I-II who are scheduled to undergo an elective laparoscopic procedure with benign gynecologic indication can participate. Following informed consent, participants are randomly allocated into two groups at the end of the surgical procedure. In the intervention group, the upper abdomen is filled with normal saline infusion with the patient in the Trendelenburg position. Then the anesthesiologist performs a standardized pulmonary recruitment maneuver with a pressure of 40 cm H_2_O. The trocar sleeve valves will be left open, so carbon dioxide can escape the abdominal cavity. With the patient in a neutral position the instruments are removed from the abdomen. In the control group, carbon dioxide is removed from the abdominal cavity at the end of surgery, with gentle abdominal pressure and passive exsufflation through the port sites, with open sleeve valves.

The primary outcomes are the incidence and intensity of post-laparoscopic pain in the shoulder, upper abdomen and at the operation sites, at 8, 24 and 48 h after surgery. Secondary outcomes are postoperative use of analgesics, nausea, vomiting and pulmonary complications.

**Discussion:**

This study may reduce post-laparoscopic pain in women undergoing laparoscopy.

**Trial registration:**

Dutch trial register, number NTR4812.

## Background

Laparoscopic surgery has become a common surgical practice. It is associated with a shorter hospital stay, earlier return to daily activities and work and improved cosmetic results compared with open procedures [1]. Despite these advantages, many patients suffer from pain in the shoulder and upper abdomen after laparoscopy. The incidence of shoulder pain ranges from 35 to 80% [2–8].

Sometimes this post-laparoscopic shoulder pain surpasses the pain at the incision site [6]. Nowadays, due to early discharge, post-laparoscopic pain will not be noticed by the physicians and therefore not treated properly.

The cause of post-laparoscopic pain is not fully understood. Several factors may contribute to this pain. Rapid distention of the peritoneum may result in traumatic traction on blood vessels and nerves with inflammatory mediator release and phrenic nerve neuropraxia [9–11]. Therefore pressure peaks and prolonged insufflations should be avoided [5, 10]. In addition, the phrenic nerve may be damaged by the acidotic and cooling effect of insufflated carbon dioxide. This may result in an irritative effect on the peritoneum and diaphragm [10, 12–15]. Furthermore, post-laparoscopic pain is thought to be caused by retention of carbon dioxide in the abdomen, which irritates the phrenic nerve and diaphragm and causes referred pain in the shoulder and pain in the upper abdomen [2, 9, 10, 16]. A significant correlation between the amount of residual pneumoperitoneum and pain scores has been reported [2, 9, 16]. It is not clear whether the length of the surgical procedure has an effect on the intensity or incidence of post-laparoscopic pain [17, 18].

Two promising strategies to reduce post-laparoscopic pain after gynecological surgery are mentioned in the literature [1, 19, 20]. The first strategy, the pulmonary recruitment maneuver, is designed to open alveoli, which increases intrapulmonary pressure. As a result, intraperitoneal pressure will rise and facilitate the removal of residual carbon dioxide from the abdomen [7, 19–22]. A second strategy involves the use of intraperitoneal normal saline. By filling the abdomen with warmed normal saline, carbon dioxide rises and escapes through the port sites [23]. In addition, normal saline is thought to offer a physiologic buffer system to dissolve excess carbon dioxide [19]. A combination of the two techniques described above has been shown to reduce post-laparoscopic pain in Asian women with a mean body weight < 60 kg [20].

We propose a randomized controlled trial to study the effect of a combination of intraperitoneal saline and the pulmonary recruitment maneuver on the incidence and intensity of post-laparoscopic pain in Dutch women.

## Methods/design

### Objective

The aim of this study is to assess the incidence and intensity of post-laparoscopic pain in the shoulder, upper abdomen and at the operating site 8, 24 and 48 h after elective gynecologic laparoscopic surgery with benign indication. This study will also evaluate postoperative use of analgesics, occurrence of nausea and vomiting and pulmonary complications.

### Trial design

This study is a randomized controlled trial and will be performed at the Maastricht University Medical Center, a university hospital in the Netherlands, and at Máxima Medical Center Veldhoven, a tertiary teaching hospital in the Netherlands.

The study is conducted according to the principles of the Declaration of Helsinki and in accordance with the Medical Research Involving Human Subjects Act (WMO) and has been approved by the ethics committee of Máxima Medical Center (METC no 1445, CCMO no NL50655.015.14). The protocol is registered in the Dutch Trial register, number NTR4812.

The trial will be conducted without any funding sources.

### Eligibility criteria

Women between 18 and 65 years of age with an American Society of Anesthesiologists physical status classification of I-II (ASA classification) who are scheduled to undergo an elective laparoscopic procedure, with a benign gynecologic indication, can participate in the trial.

The first exclusion criterion is daily use of analgesics because postoperative use of analgesics is a secondary outcome. The next exclusion criterion is allergy/intolerance to nonsteroidal anti-inflammatory drugs (NSAIDs), as these are the standard postoperative analgesics used. Emphysema and chronic obstructive pulmonary disease (COPD) are also exclusion criteria for the pulmonary recruitment maneuver is used. A midline laparotomy in the medical history is another exclusion criterion, as this is often a reason to perform an open laparoscopy and it increases the risk of conversion to laparotomy. The last exclusion criterion is poor understanding of the Dutch language. This was deemed necessary because we make use of questionnaires written in Dutch.

### Patient recruitment, randomization and collection of data

Eligible patients are identified by the gynecologist or the resident in one of the two participating hospitals. Women eligible for the trial will be counseled by experienced research nurses or researchers. They will be informed about the aims, methods, reasonably anticipated benefits and potential hazards of the study. After a week patients will be asked if they want to participate and informed consent will be collected. By giving written informed consent, patients agree to participate and agree that their anonymous data may be used for publication.

Randomization will be performed by using sealed envelopes and will take place just before the end of the surgery.

The study is blinded for patients, but not for the gynecologist, as the gynecologist is the one who will leave normal saline intraperitoneal when necessary. Because this study is a multicenter trial, randomization will be stratified by hospital to get an equal distribution of patients between the two groups (control and intervention) per hospital. For randomization we used an Excel sheet that randomly assigned 200 patients (two lists of 100 patients, one for each hospital) to either the intervention or control group. Data handling will be done anonymously and the date code is only available to the local investigator. The baseline data and follow-up data collection at both hospitals is the responsibility of the two local investigators. Data will be stored in a sealed, anonymous files.

The dataset supporting the conclusions of this article will be available upon request. In accordance with the guidelines of the Dutch Federation of University Medical Centers (NFU), the data will be kept for 15 years.

### Interventions

In the intervention group, the patient will be placed in the Trendelenburg position of 30 degrees at the end of the laparoscopic procedure. An intraperitoneal saline infusion of 15–20 ml/kg will be administered evenly and bilaterally by the operating gynecologist. The anesthesiologist will perform the pulmonary recruitment maneuver after the saline infusion. Five pulmonary insufflations with a pressure of 40 cm H_2_O (pulmonary recruitment maneuver) will be given. The fifth positive pressure inflation will be held for 5 sec﻿. The trocar sleeve valves will be left fully open during this procedure, so the carbon dioxide can escape the abdominal cavity. Hereafter the patient is placed in a neutral position and the instruments are removed from the abdomen.

In the control group, the carbon dioxide is removed from the abdominal cavity at the end of surgery, with gentle abdominal pressure and passive exsufflation through the port sites with the sleeve valves open.

### Measurement and follow-up

Primary outcomes are the incidence and intensity of post-laparoscopic pain in shoulder, upper abdomen and at the operating site at 8, 24 and 48 h after surgery, which are measured using the Visual Analogue Scale (VAS). Secondary outcomes are postoperative use of analgesics, nausea, vomiting and pulmonary complications. We will record patient characteristics (age, height, weight, body mass index (BMI)) and operative details (type of surgery, ASA-classification, duration of surgery, estimated blood loss, total volume of gas used, amount of normal saline left intraperitoneal, and postoperative hospital stay).

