### Statistical analysis

#### Sample size

The two primary outcomes of our study are the incidence of pain and the intensity of pain using the VAS score. In accordance with Tsai et al. [20], we have measured pain intensity using the preliminary data of the 24-h and 48-h pain scores. Post-laparoscopic pain is most common and evident in the first 48 h after surgery, after that the pain declines. That is why we have chosen to look at the 48-h pain score. Furthermore, we have assumed a reduction in the incidence of pain from 80% to 50% using this combination treatment compared to standard treatment [7, 24]. A dropout rate of 20% is anticipated because of loss to follow-up or incomplete questionnaires. We use Fisher’s exact test to test for differences in the proportion. To do so, we need to include at least 126 patients (63 women in each study arm) to obtain a power of 85% when testing with an alpha of 5%.

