#### Data analysis

Data will be analyzed according to the intention–to-treat principle. Statistical analysis will be performed using the software Statistical Package for the Social Sciences 22.

Categorical variables will be described as frequencies and percentages. Continuous variables will be described in terms of means with standard deviation if normally distributed, and otherwise as a median with an interquartile range (IQR). Significance will be tested two sided with an α-level of 0.05. Patients will be classified as either having pain or not having pain using the questionnaires the patients fill in after surgery. To compare the incidence of pain between the intervention and control groups, the Pearson’s Chi-squared statistic will be used. For those patients experiencing pain, the average pain scores between groups will be compared. T-tests for pain scores will be used when the scores are normally distributed.

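### The primary outcome is defined in conflicting ways (18 comparisons, or two outcomes, or the 48-h score), so the stated 5% error rate and 85% power hold for only one unspecified comparison

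*Protocol article*

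**What the plan says.** **Measurement and follow-up** gives the wide definition: "Primary outcomes are the incidence and intensity of post-laparoscopic pain in shoulder, upper abdomen and at the operating site", at 8, 24 and 48 h. The Abstract lists the same measures, sites and times as primary. The Objective repeats them as the aim of the study: "pain in the shoulder, upper abdomen and at the operating site 8, 24 and 48 h after elective gynecologic laparoscopic surgery".

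**Sample size** gives a narrower one: "The two primary outcomes of our study are the incidence of pain and the intensity of pain using the VAS score". It names no site. After explaining why the first two days matter, it adds: "That is why we have chosen to look at the 48-h pain score". The calculation then rests on a single incidence of pain, falling from 80% to 50%, tested with Fisher's exact test at 5% with 85% power, giving 63 women per arm. On attrition it says: "A dropout rate of 20% is anticipated because of loss to follow-up or incomplete questionnaires".

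**Data analysis** sets the level once: "Significance will be tested two sided with an α-level of 0.05". It plans Pearson's chi-squared test for incidence and a comparison of mean scores among the patients who have pain. It does not order the comparisons, divide the 5% between them, or say which result decides the trial.

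**The concern.** A reader cannot tell whether the trial has 18 primary comparisons, six (three sites and two measures at 48 h), two, or one. Each reading leads to a different claim from the same data.

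Two stated properties depend on the answer. The 5% level protects the trial's conclusion only if a single comparison carries it. The 85% power belongs to one incidence comparison whose site is not given and whose time is at best implied.

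Timing makes this more pressing. The Results section reports 56 + 71 = 127 women already included when the target was raised to 200. The longer the deciding comparison stays open, the harder it is to show that it was not chosen with results in view.

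**Working it through.** **1. The plan's own figure.** Inputs from Sample size: 80% vs 50%, Fisher's exact test, alpha 0.05 (two-sided, from Data analysis), power 85%, dropout 20%. Exact enumeration gives power of 84.2% with 49 evaluable per arm and 85.3% with 50, so 50 are needed. Then 50 / (1 − 0.20) = 62.5, rounded up to 63 per arm, 126 in total. The stated figure reproduces for one comparison at the full 5%.

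**2. Number of primary comparisons on each reading.**
- Measurement and follow-up: 2 × 3 × 3 = 18
- 48 h only, all sites: 2 × 3 = 6
- Two primary outcomes: 2
- The comparison that was powered: 1

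**3. Chance of at least one false positive, independent tests at 0.05.** Formula: 1 − 0.95^k.
- k = 18: 1 − 0.95^18 = 60.3%
- k = 6: 1 − 0.95^6 = 26.5%
- k = 2: 1 − 0.95^2 = 9.75%
- k = 1: 5%

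**4. Allowing for correlation.** The same women are scored at every site and time, so the tests will be positively correlated. The article gives no correlation; the values below are assumptions. Two models were used.

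*(a) Correlation set between patients' underlying pain scores.* Nine correlated scores per woman, 80 per arm, no true effect, assumed pain prevalence 65%, Pearson tests for incidence, t-tests among those with pain, all 18 tests:

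| Site correlation | Time correlation | At least one p < 0.05 |
|---|---|---|
| 0.3 | 0.5 | 58% |
| 0.3 | 0.8 | 53% |
| 0.6 | 0.5 | 55% |
| 0.6 | 0.8 | 49% |
| 0.8 | 0.8 | 46% |
| 0.9 | 0.9 | 38% |

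*(b) Correlation set directly between the test statistics.* With sites 0.2–0.5, times 0.5–0.8 and incidence–intensity 0–0.5, the 18-test figure is 39% to 54%. With one equal correlation throughout it is 51% at 0.3, 40% at 0.5, 28% at 0.7 and 15% at 0.9.

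The models differ because classifying women as having pain or not, and comparing intensity only among those with pain, weakens the link between tests. A given correlation in scores therefore means a smaller one between test statistics.

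For the six tests at 48 h, model (a) gives about 23–26%; model (b) with equal correlation gives 24% at 0.3 and 21% at 0.5. For two tests, model (b) gives 9.1% at 0.5.

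**5. Power if all 18 stay primary.** The strictest step of Holm is 0.05 / 18 = 0.00278. For 80% vs 50%:
- 50 evaluable per arm (the original plan): Fisher 50%, Pearson 58%
- 80 evaluable per arm (the 100 per arm in Results, less 20%): Fisher 82%, Pearson 85%

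Both tests are shown because Sample size names Fisher's and Data analysis names Pearson's. With a single primary comparison at 0.05 and 80 per arm, Fisher's power is 97.5%.

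**The case against.** The strongest reply concerns scope. This is a journal article; a multiplicity rule or testing order commonly sits in a full protocol or analysis plan that is not shown. The 0.05 in Data analysis may be only a general significance level. That stands: the missing adjustment is not a fault by itself. It does not remove the conflict between the article's own sections. Whatever definition an unseen plan adopts, it would disagree with either Measurement and follow-up or Sample size.

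A second reply is that no single false-positive rate can be read from the article, and that also stands. A reader might infer that the trial has a 50–60% chance of a false positive primary result. The documents do not support this as a fact: it needs all 18 comparisons to be tested, any one to count as success, and fairly weak correlation between tests. The article states none of these, and 60% is the ceiling for independent tests. It also ignores the narrower readings that Sample size allows.

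Third, the 48-h remark may describe the period in which pain is most evident, not a sole primary time. The wording permits either, which is part of the problem.

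Fourth, a reader might infer that the 80% to 50% assumption refers to the shoulder, since 80% is the top of the shoulder-pain range in the Background. Sample size names no site, so this is not established.

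**Conclusion.** The concern holds as an internal contradiction over what is primary, with direct consequences for the error rate and power. If any significant primary comparison may be claimed as a positive result, the chance of a false positive is at most about 60% on the 18-comparison reading, and roughly 40–58% under assumed moderate to strong correlation (less if the test statistics are very highly correlated). It is about 21–26% on the 48-h reading and about 10% on the two-outcome reading. Only a single comparison keeps the stated 5%.

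The sample-size arithmetic is correct, but it serves one comparison that the article does not fully identify. Nothing in the article supports an 80% vs 50% effect at every site and time, and it gives no inputs for the power of the intensity comparisons. Nor does it show that a result has been selectively claimed; the point is that the definition leaves room for it.

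**What to change.** Issue a dated amendment, prepared without sight of outcome data by arm, that names one primary outcome: one measure, one site, one time. Incidence of shoulder pain at 48 h, with pain classified from the questionnaire as Data analysis describes, would serve as an example; the choice is the sponsor's. Make the other sites and times, and intensity, secondary, or test them in a fixed order or under Holm. Bring the Abstract, Objective, Measurement and follow-up, and Sample size sections into line with that choice, and state the site and time to which the 80% vs 50% assumption applies.

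If all 18 are to remain primary, apply Holm across them and restate the power at 0.05/18: about 82% (Fisher) or 85% (Pearson) with 80 evaluable per arm for a comparison with the full assumed effect, and about 50% (Fisher) with 50 per arm.

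Cost: an amendment and consistent wording, with no extra patients for a single primary outcome. The downside is that the remaining comparisons lose unadjusted claims of significance.

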### Statistical analysis

#### Sample size

The two primary outcomes of our study are the incidence of pain and the intensity of pain using the VAS score. In accordance with Tsai et al. [20], we have measured pain intensity using the preliminary data of the 24-h and 48-h pain scores. Post-laparoscopic pain is most common and evident in the first 48 h after surgery, after that the pain declines. That is why we have chosen to look at the 48-h pain score. Furthermore, we have assumed a reduction in the incidence of pain from 80% to 50% using this combination treatment compared to standard treatment [7, 24]. A dropout rate of 20% is anticipated because of loss to follow-up or incomplete questionnaires. We use Fisher’s exact test to test for differences in the proportion. To do so, we need to include at least 126 patients (63 women in each study arm) to obtain a power of 85% when testing with an alpha of 5%.

#### Data analysis

Data will be analyzed according to the intention–to-treat principle. Statistical analysis will be performed using the software Statistical Package for the Social Sciences 22.

Categorical variables will be described as frequencies and percentages. Continuous variables will be described in terms of means with standard deviation if normally distributed, and otherwise as a median with an interquartile range (IQR). Significance will be tested two sided with an α-level of 0.05. Patients will be classified as either having pain or not having pain using the questionnaires the patients fill in after surgery. To compare the incidence of pain between the intervention and control groups, the Pearson’s Chi-squared statistic will be used. For those patients experiencing pain, the average pain scores between groups will be compared. T-tests for pain scores will be used when the scores are normally distributed.

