## Discussion

In light of the increasing number of laparoscopic interventions [25], the short postoperative stay of patients and the high incidence of post-laparoscopic shoulder and upper abdominal pain [2–8], interventions to decrease post-laparoscopic pain are important and necessary in order to deliver good medical care. The combination of intraperitoneal saline infusion and the pulmonary recruitment maneuver has shown to decrease post-laparoscopic pain in Asian women with a mean body weight < 60 kg [20]. This study will be performed in the Netherlands in a population of West-European women with a higher average BMI, who will undergo a gynecologic laparoscopy for benign indication. The results will therefore be applicable for a large population of patients undergoing elective benign laparoscopy.

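### The named tests for pain incidence and intensity ignore hospital and other variables fixed before allocation; a pre-specified adjusted analysis would be a cheap improvement, of modest and uncertain size.

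*Protocol article*

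**What the plan says.** The Data analysis section of the protocol article names the tests. The method given "To compare the incidence of pain between the intervention and control groups" is Pearson's chi-squared. Mean pain scores are then compared among women who have pain, by t-test if the scores are normally distributed. "Significance will be tested two sided with an α-level of 0.05". No covariate appears in either comparison.

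Three other sections bear on this:

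- Measurement and follow-up lists what is recorded: age, height, weight and BMI, and "operative details (type of surgery, ASA-classification, duration of surgery" among other items.
- Patient recruitment, randomization and collection of data says that randomization is stratified by hospital and "will take place just before the end of the surgery".
- Results reports 71 intervention and 56 control women, attributes the inequality to randomizing without blocks, and gives the further recruitment needed to reach 100 per arm as 29 and 44.

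**The concern.** Type of surgery, BMI and age are already collected. Allocation comes so late that all three are settled beforehand, so adjusting for them cannot introduce bias from events after randomization. Any elective benign gynaecological laparoscopy is eligible, so case mix may vary. Hospital was used to stratify the allocation but is absent from the analysis.

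Two things are at stake. If these variables predict pain, the unadjusted comparison has a wider interval than the same data could give. And the arms were filled in different proportions before and after the amendment, so a change over time in case mix or pain reporting would pass in part into an unadjusted difference between arms.

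**Working it through.** **1. Reproduce the plan's own figure.** Inputs from Sample size: "we have assumed a reduction in the incidence of pain from 80% to 50" per cent, Fisher's exact test, 85% power, alpha 5%, and "A dropout rate of 20% is anticipated because of loss to follow-up or incomplete questionnaires". Enumerating the exact power of Fisher's test gives 84.2% at 49 per arm and 85.3% at 50. Inflating for dropout, 50 / (1 − 0.20) = 62.5, rounded up to 63 per arm and 126 in total. This matches the article's statement: "we need to include at least 126 patients (63 women in each study arm) to obtain a power of 85% when testing with an alpha". The figure rests on an unadjusted test and needs no help from covariates.

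**2. Power of the test actually named for incidence.** Pearson's chi-squared at 80% vs 50% has exact power 89.5% with 50 evaluable per arm. With 200 enrolled and 20% dropout, 100 × 0.80 = 80 are evaluable per arm, and power is 98.3%.

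**3. Effect of adjustment on incidence.** The article gives no prognostic strength, so R² on the latent logistic scale is an assumption and a range is shown. Each row comes from 4,000 simulated trials at 80% vs 50% with 50 evaluable per arm. Chi-squared is compared with a logistic model on arm, BMI and a three-level type of surgery. The variance ratio is for the standardised risk difference against the crude one.

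| Assumed R² | Variance ratio | Power, unadjusted | Power, adjusted |
|---|---|---|---|
| 0 | 1.04 | 88.4% | 87.9% |
| 0.05 | 1.00 | 89.5% | 90.1% |
| 0.10 | 0.96 | 89.5% | 90.8% |
| 0.20 | 0.90 | 89.0% | 92.5% |
| 0.30 | 0.83 | 89.7% | 94.2% |

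With 80 evaluable per arm, power is about 98 to 99% either way. The simulated model had no hospital, age or period term. Each extra term without prognostic value would add a little to the cost in the first row.

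**4. Effect on intensity.** For a linear model the residual variance falls by the factor (1 − R²), so interval width falls by 1 − √(1 − R²):

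- R² = 0.10: 1 − √0.90 = 5.1%
- R² = 0.20: 1 − √0.80 = 10.6%

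The comparison covers only women with pain. At the plan's rates and 80 evaluable per arm, that is 80 × 0.80 = 64 controls and 80 × 0.50 = 40 intervention women. For an assumed true difference of 0.4 SD, the t-test's noncentrality is 0.4 / √(1/64 + 1/40) = 1.98 and power is about 50%. Dividing 0.4 by √(1 − R²) gives 0.422 at R² = 0.10 (power 54%) and 0.447 at R² = 0.20 (power 59%).

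**5. The two periods.** The intervention share was 71/127 = 56% before the amendment, and 29/73 = 40% is what was needed after it. If both arms reach 100, 71% of intervention women and 56% of controls come from the first period, a gap of 15 points. A difference in pain between periods would enter the crude comparison multiplied by 0.15. Surgery type, BMI and age remove only the part that they explain. A period term addresses it directly.

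**The case against.** The strongest reply is that nothing here is wrong. The named tests are valid without covariates, the sample size was built on an unadjusted test, and chance imbalance in case mix is already allowed for in the test's error rate and interval. An article condenses a fuller plan, and adjusted analyses often sit in a document not shown here. All of that stands, except that the article does not leave the method open: it names the tests, so the suggestion concerns a stated choice.

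A reader might infer that precision is being given away for nothing, or that adjustment is a free gain. The article does not support this. No section says that type of surgery, BMI or age predicts this pain. Background discusses one candidate factor, length of surgery, and calls its effect unclear. The reference to "a population of West-European women with a higher average BMI" in the Discussion contrasts this population with the earlier trial's; it is not evidence that BMI predicts pain within this one. With uninformative covariates, adjustment costs a little.

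A reader might also expect intensity power to rise from 71% to 76–80%. Those figures hold for 0.4 SD with 80 women per arm in the comparison, but the plan compares only those with pain, about 64 and 40.

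Finally, the amendment argument cannot be used to support a model that has no period term.

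**Conclusion.** The point holds as a minor, low-cost improvement. The named comparisons leave out the stratification factor and recorded variables fixed before allocation. That makes them neither invalid nor, for incidence on the plan's own assumptions, underpowered.

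For incidence the likely effect is small: a variance change from about +4% to −10% over an assumed R² of 0 to 0.20 at 50 evaluable per arm, and almost nothing in power at 80. It matters more for intensity, which is also primary and where power may be only about 50%. There the gain is roughly 4 to 9 points, given an assumed 0.4 SD and R² of 0.10 to 0.20. The best-grounded terms come from the design itself: hospital, because allocation was stratified by it, and period, because the allocation ratio changed. Adjustment does not cure the comparison of intensity only among women with pain, a subset formed after randomization.

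**What to change.** Make the main incidence analysis a logistic regression on:

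- arm;
- hospital;
- before or after the amendment;
- type of surgery, in two or three classes;
- BMI and age.

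Fix the list and the surgery classes before the data are opened. Report the standardised risk difference with a 95% interval. Use the same covariates in the intensity model. Keep the chi-squared test and t-tests as a sensitivity analysis. Leave out duration of surgery and volume of saline left in the abdomen, because both are partly determined after allocation.

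The cost is wording in the analysis plan. No new measurements are needed, since the covariates are already recorded and period follows from when each woman was enrolled. The one statistical downside is a small possible loss of precision if the covariates turn out not to be prognostic, which is a reason to keep the list short.
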